**PROTOCOL HISTORY**

*Use the table below to summarize modifications and amendments to protocol that have been approved by [name] (Principal Investigator).*

| **Protocol Version Date** | **Protocol Type** *(Original, Amendment)* |
| --- | --- |
| **v1.30.2024** | **Original Protocol** |
| **v10.4.2024** | **Revised Protocol** |

# SCHEMA

**Inclusion:**

- Men with newly diagnosed, non-metastatic intermediate risk prostate cancer with features on mpMRI Bx:
  - Histopathologic diagnosis GG 2 or, have a of GG 3 and PSA <20 ng/mL

**Exclusion**

- Received any treatment for prostate cancer except for ≤6 months of conventional ADT
- Contraindications to focal ablation of the prostate
- Subjects with locally advanced, nodal, or metastatic prostate cancer

**Treatment arm: Androgen Deprivation Therapy**

8-12 weeks from

ADT start = Focal Therapy

Primary: To determine the proportion of men with CSPCa (GG ≥2) in the ablated prostate and unablated tissue by performing a surveillance mpMRI and MRI-TB at 12-months following prostate focal ablation

Other: Safety of the combination, Change in QOL factors (sexual function), PSA Kinetics

**N = 57**

**Treatment duration: 3 months**

**Follow-up period: 12 months after Focal Therapy**

# STUDY ABBREVIATIONS

The following are common terms and abbreviations and acronyms used throughout this protocol. The terms “focal therapy,” “focal prostate ablation,” and “prostate ablation” are considered to be interchangeable for purpose of this trial.

| **Abbreviation** | **Term/Description** |
| --- | --- |
| **ADT** | Androgen Deprivation Therapy – any generic LHRH |
| **AE** | Adverse Event |
| **AR** | Androgen Receptor |
| **BS** | Bone Scan |
| **CBC** | Complete Blood Count |
| **CMP** | Complete Metabolic Panel |
| **ConMed** | Concomitant medication |
| **CS / NCS** | Clinically significant / Not clinically significant |
| **CSPCa** | Clinically significant prostate cancer |
| **CTAP** | Computed tomography arterial portography |
| **CTCAE** | Common Terminology Criteria for Adverse Events |
| **ECOG** | Eastern Cooperative Oncology Group, a Performance Scale |
| **EDC** | Electronic Data Capture – REDCap system in use for this study |
| **EOT** | End of Treatment |
| **EPE** | Extraprostatic extension |
| **EPIC-26** | Expanded Prostate cancer Index Composite short form questionnaire |
| **FT** | Focal Therapy ablation of the prostate |
| **GG** | Grade Group and not “Gleason grade” which refers to the older system of Gleason sum (6-10) |
| **HIFU** | High-Intensity Focused Ultrasound |
| **HRQoL** | Health related quality of life |
| **I-PSS** | International prostate symptom score |
| **LHRH** | Luteinizing hormone-releasing hormone |
| **LTFU** | Long term follow-up |
| **mpMRI** | Multiparametric magnetic resonance imaging |
| **MRI-TB** | Magnetic resonance imaging targeted biopsy |
| **PCa** | Prostate cancer |
| **PFS** | Progression free survival |
| **PI** | Principal investigator |
| **PI-RADS** | Prostate Imaging Reporting & Data System |
| **PSA** | Prostate Specific Antigen |
| **PE** | Physical Exam |
| **RT** | Radiation Therapy |
| **SAE** | Serious Adverse Event |
| **SHIM** | Sexual Health Inventory for Men |
| **SOC** | Standard of Care – per institution |
| **TPM** | Template mapping biopsies |
| **UA** | Urinalysis |
| **CTSO** | Clinical Trial Support Office |
| **UCCCC** | University of Chicago Medicine Comprehensive Cancer Center |

# OBJECTIVES

## Primary Objectives

1. To determine the proportion of men with residual/recurrent clinically significant prostate cancer (Grade Group ≥2 disease) in the ablated or unablated prostate tissue following the combination treatment of 3-months of androgen deprivation therapy, and partial ablation of the prostate in men with newly diagnosed non-metastatic intermediate risk prostate cancer; specifically, men with a histopathologic diagnosis of Grade Group 2 & 3, with prostate specific antigen level <20 ng/mL.
2. To assess the safety of the combination treatment of androgen deprivation therapy and partial ablation of the prostate for the management of patients with newly diagnosed non-metastatic intermediate risk prostate cancer; specifically, men with a histopathologic diagnosis of Grade Group 2 & 3, with prostate specific antigen level <20 ng/mL using the common terminology criteria for adverse events.

## Secondary Objectives

1. To assess the genitourinary side effect profile of the combination treatment of androgen deprivation therapy, and partial ablation of the prostate as it pertains to lower urinary tract symptoms and sexual function based on health-related quality of life measures.

1. To determine the prostate specific antigen response following treatment with androgen deprivation therapy, and partial ablation of the prostate.
2. To determine the proportion of men converting to whole gland therapy (radical prostatectomy or radiation therapy) and/or requiring systemic therapy and/or developing metastases and/or dying of prostate cancer during the course of study.
3. To determine the proportion of men with absence of any cancer in the ablated or unablated prostate tissue on post treatment prostate biopsy.
4. To determine the proportion of men with baseline normal serum testosterone who have achieved testosterone recovery over the course of the study and follow-up period.

## Exploratory Objectives

1. To prospectively obtain tissue and blood for biobanking for use in future potential analysis or research on prostate cancer.

# BACKGROUND

## Prostate Cancer Background

The burden of prostate cancer (PCa) remains significant, with estimates of approximately 248,530 new diagnoses and 34,130 deaths from PCa in 2021.^1^ It is estimated that men with intermediate-risk and high-risk disease (Grade Group (GG) ≥3) represent 37-39% and 26-28% of all PCa patients, respectively.^2^ A majority of these patients undergo whole gland intervention, such as radiation therapy (RT) with androgen deprivation therapy (ADT) or radical prostatectomy, which results in significant treatment related morbidity.^3^ The impact of said treatments on genitourinary and sexual function can result in devastating changes in quality of life. Furthermore, a significant proportion of these patients can have yet unidentified micro-metastatic lesions that may progress to clinically or radiologically confirmed disseminated disease; thus, the risk of morbidities of a primary radical whole gland intervention may outweigh the benefit attained.

In the past decade, partial ablation of the prostate, or focal therapy (FT), has become a feasible treatment option for select men with biopsy proven clinically significant PCa (CSPCa) confined to a portion of the prostate. FT is delivered via a variety of modalities including cryoablation, high-intensity focused ultrasound (HIFU), and irreversible electroporation. In contrast to whole gland treatment, FT considers the spatial distribution of PCa within the prostate for ablation, thus a fraction of tissue is destroyed to facilitate preservation of genitourinary function.^4^

## Prostate Cryoablation and High-Intensity Focused Ultrasound Ablation for Focal Therapy Treatment of Prostate Cancer

Cryoablation, or tissue destruction by freezing, has been used as an alternative to surgical resection for decades.^5-8^ Cryoablation of the entire prostate has shown durable results for primary treatment and utilized as salvage treatment after primary RT for PCa.^9^ Studies of FT cryoablation have demonstrated a reduced rate of urinary incontinence and >80% preservation of erectile function.^10^ Oishi et al.^11^ prospectively evaluated 160 men who underwent cryoablation of localized PCa for oncologic and functional outcomes. Their primary endpoint was treatment failure-free survival, which was defined as requiring any radical and or whole gland treatment, initiation of systemic therapy, biochemical failure (increase of 2 ng/mL above the PSA nadir) or PCa specific mortality. Twenty-five men (16%) had high-risk PCa, 106 men (66%) had intermediate-risk and 29 men (18%) had low-risk PCa with an overall median baseline PSA of 6.3 ng/mL and follow-up of 40-months. Of note, 28 patients (17 intermediate-risk and 11 high-risk) received neoadjuvant ADT prior to FT for a median of 12-months. Transrectal ultrasound guided prostate biopsy was recommended at 1-year after FT cryoablation; however, 104 men ultimately underwent post-procedural prostate biopsy. The authors estimated that 5-year treatment failure-free survival, metastasis-free survival, cancer specific and overall survival were 85%, 100%, 100% and 100%, respectively. The 5-year CSPCa, i.e., GG ≥2, free survival was 87%, 74% and 64% for low-, intermediate- and high-risk subjects who underwent a post-procedural biopsy, respectively. Continence and potency were reported in 97% and 73% of patients, respectively, within 2-years of FT.

Shah et al.^12^ performed a systematic review of literature from 2006-2014 regarding FT cryoablation treatment of PCa. They included 9 studies with 1582 patients that underwent FT. All studies were case series with no control group. A sub-group analysis of 759 patients (48%) had intermediate- (~80%) or high-risk (~20%) disease based on transrectal or transperineal prostate biopsy with follow-up ranging from 9- to 70-months. The authors reported a rate of biochemical recurrence free survival of 72 to 93% over the follow-up period based on an increase of 2 ng/mL above nadir PSA or three consecutive increases in PSA from nadir following FT. Of the 291 patients that had post-procedural biopsy, 98 men (25%) were found to have residual PCa, but ~68 specimens were identified as GG1disease on the contralateral untreated portion of the prostate. Patient report of incontinence ranged from 0 to 4% and erectile dysfunction ranged from 0 to 42%.

Tay et al.^13^ provided recommendations for patient management based on a consensus panel of 47 international experts in FT. The panel endorsed the treatment of GG1, GG2 and GG3 disease using FT and provided tumor volume thresholds as guidance for patient selection. In addition, multiparametric magnetic resonance imaging (mpMRI) and combined systematic and mpMRI targeted prostate biopsy (MRI-TB) were deemed standard imaging and diagnostic testing necessary for FT candidacy. Lebastchi et al.^14^ assimilated an international expert panel and agreed that mpMRI is the preferred imaging modality for identifying the treatment response of FT, provided a definition and recommendations for patient follow-up, and suggested that MRI-TB within 1-year of FT to evaluate the treated and untreated prostate tissue should be standard practice.

HIFU is an FDA approved minimally-invasive procedure used as a targeted approach to treat low- to intermediate-risk PCa.^15, 16^ The focused ultrasound energy delivered to the prostate results in mechanical and thermal injury and cavitation of the tissue. The mechanical energy is converted into heat causing hyperthermia above 65°C leading to coagulative necrosis.^17-19^ HIFU can be used for partial as well as whole gland treatment of PCa and is currently the most commonly used energy modality for focal therapy of prostate cancer in US due to excellent functional outcomes in terms of erections and continence.Click or tap here to enter text.^20^ Stabile et al reported one of the largest experience of HIFU used for focal treatment of prostate cancer in 2019. Majority of their patients receiving focal HIFU had intermediate risk prostate cancer with only a small proportion having low risk prostate cancer. While not everyone got a repeat biopsy, 25% of the total population was found to have CS cancer on repeat biopsy. However, 91% of the men avoided radical therapy at 5 years highlighting the excellent oncological outcomes of focal HIFU in short and intermediate term. HIFU is also used as a salvage therapy following biochemical recurrence after radiation therapy for PCa.Click or tap here to enter text.^21^ HIFU has also been used along with ADT as first line salvage therapy for local recurrent Pca.^22, 23^Click or tap here to enter text.

There are limitations to FT.^24^ The location of the PCa lesion can affect treatment related morbidity, e.g., its proximity to the urethra and or rectum risks the rare complication of genitourinary fistula. There is yet undetermined consensus with respect to appropriateness of patient selection for PSA thresholds beyond 10 ng/mL. Long-term follow-up and outcomes of FT are currently under study and ultimately necessary to facilitate creation of practice guidelines. Compliance with routine and long-term follow-up, including repeat prostate biopsy following FT, is necessary and can affect patient selection, especially if there is concern a patient will be non-compliant. The appropriateness of FT may be limited to patient performance status and life expectancy, with expert opinion suggesting intermediate-risk PCa treatment guidelines be followed in this regard.

## Rationale for the Combination of Focal Therapy with Androgen Deprivation Therapy

Given a greater risk of local recurrence^17^, the majority of patient selection for FT is reserved for low- or favorable intermediate-risk PCa.^10^ Patients with unfavorable intermediate-risk PCa are offered FT often in the context of experimentation due to the more aggressive nature of their disease and concern for local or distant treatment failure.

The use of whole gland ablation for non-metastatic PCa in combination with ADT has previously been studied. Donnelly et al.^25^ randomized 244 patients with intermediate- and high-risk PCa to 3-months of neoadjuvant ADT with RT or whole gland cryoablation and reported similar overall and biochemical recurrence free survival between interventions and decreased PCa identified at surveillance 36-month prostate biopsy for patients who underwent ablation. Chin et al.^26^ randomized 64 men to 6-months of perioperative ADT and RT (n=31) or whole gland cryoablation (n=33) and reported similar disease-specific and overall survival between the two treatments. Thus, efforts to manage intermediate-risk or greater risk classifications of PCa utilizing FT would require a multimodal approach and could lead to similar survival rates as radical treatment.

We believe that the effective androgen blockade will augment the oncologic success of FT. Herein, our objective is to investigate the safety and efficacy of combining ADT and partial ablation of the prostate for the treatment of intermediate -risk PCa.

## Correlative Studies Background

Given this novel combination therapy, we wish to obtain core tissue samples at the time of FT for biospecimen banking and potential future analysis and research on PCa. Two 18-gauge biopsy cores will be collected from the target area(s) and one each from peritumoral and untreated prostate for exploratory outcomes on correlatives during the FT procedure.

At the time of 12-month MRI-TB two 18-gauge biopsy cores will be collected from the ablated area(s) and one each from periablation zone and untreated prostate for exploratory outcomes on correlatives during the FT procedure.

# PATIENT SELECTION: ELIGIBILITY

## Inclusion Criteria

1. Subjects must have intermediate-risk PCa as defined by the below criteria:
   1. Favorable intermediate-risk PCa:
      1. ≤ clinical stage T2c, GG2, and PSA ≤ 10 ng/mL, and <50% positive biopsy cores with PCa
   2. Unfavorable intermediate-risk PCa:
      1. ≤ clinical stageT2c, GG2, and PSA 10-20 ng/mL, or ≥50% positive biopsy cores with PCa, or
      2. ≤ clinical stage T2c, GG3, and PSA < 20 ng/mL

Note: The PSA value for this inclusion criteria must be the value obtained just prior to the subject’s MRI-TB that provided the initial histopathologic diagnosis. This is considered to be the subject’s “baseline” PSA.

If the MRI-TB which initially diagnosed the subject’s PCa was obtained greater than 3-months from the time of study consent, then a repeat PSA should be completed for screening purposes to obtain a “baseline” PSA (unless one has been obtained for SOC at least 3-months after this initial biopsy in which case no repeat value is needed and this may be used for eligibility). This applies to all participants regardless of GG used for eligibility.

Note: The histopathologic diagnosis must be obtained via “MRI-TB”, which for the purposes of the present study, is defined as both a systematic 12-core sextant random prostate biopsy and a targeted prostate biopsy. The targeted prostate biopsy can be performed via in-bore mpMRI prostate biopsy, cognitive mpMRI/ultrasound fusion prostate biopsy or software mpMRI/ultrasound fusion prostate biopsy. This “MRI-TB” must not be obtained greater than 1 year from the date of consent. See section 6.6. for more requirements for the MRI-TB.

1. No mpMRI evidence of extra-prostatic extension (EPE) or seminal vesicle invasion, and if seminal vesical invasion is suspected, it must be excluded by prostate biopsy.
2. Subjects must have chosen to get Focal Therapy for the treatment of prostate cancer.
3. Subjects must have confirmed non-metastatic PCa following SOC screening for patients with unfavorable intermediate-risk PCa, a combination of computed tomography imaging of the abdomen and pelvis (CTAP) and technetium-99-mDP nuclear medicine bone scan (BS) and/or prostate-specific membrane antigen positron emission tomography (PSMA/PET) scan prior to enrollment. The imaging studies should be obtained within 6-months of enrollment. Additional imaging is not required for men with favorable intermediate-risk PCa. See [Section 6.7](#_Screening_Prostate_Cancer).
4. Subject must be male ≥ 18 years-old.
5. Subjects must have a life expectancy of at least 10-years per the opinion of the treating investigator.
6. Subjects must be designated as Eastern Cooperative Oncology Group (ECOG) performance status ≤ 2 or Karnofsky Performance Status Scale Score ≥ 60%, see Appendix A).
7. Subjects must be fit to undergo general anesthesia and the FT surgical procedure, which includes adequate visualization of the prostate gland on transrectal ultrasound imaging, access to the urethra, perineum and rectum, as well as be tolerant of lithotomy positioning in the opinion of the treating investigator or the operating surgeon(s) if not the same as the treating investigator.
8. Subjects must have adequate organ and marrow function as defined below:

| Hemoglobin | ≥ 10 g/dL |
| --- | --- |
| Leukocytes | ≥ 3,000/mcL |
| Absolute neutrophil count | ≥ 1,500/mcL |
| Platelets | ≥ 100,000/mcL |
| Total bilirubin | ≤ 1.5 x institutional upper limit of normal (ULN) |
| AST(SGOT)/ALT(SGPT) | ≤ 2.5 × institutional ULN |
| Creatinine | < 1.5 institutional ULN |
| OR |  |
| Calculated or measured creatinine clearance | > 50 mL/min/1.73 m^2^ |
| eGFR | >30 mL/min using the MDRD (modification of diet and renal disease) formula |
| Serum albumin | ≥3.0 g/dL |
| Serum potassium | ≥3.5 mmol/L |

1. Subjects with a prior or concurrent malignancy whose natural history or treatment does not have the potential to interfere with the safety or efficacy assessment of the investigational regimen are eligible for this trial.
2. Subjects who are sexually active with a woman of childbearing potential must agree to use a condom with spermicidal foam/gel/film/cream/suppository and his partner must also be practicing a highly effective method of contraception (i.e., established use of oral, injected or implanted hormonal methods of contraception; placement of an intrauterine device or intrauterine system) during treatment and for 3-months following the last ADT treatment.
3. Ability to understand and the willingness to sign a written informed consent document.

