# STATISTICAL CONSIDERATIONS

## Study Design/Endpoints

This study will be a multi-institutional single arm phase I/II trial with a recruitment goal of 57 patients with treatment naïve non-metastatic intermediate-risk PCa.

Primary endpoints

1. To determine the proportion of men with CSPCa (GG ≥2) in the ablated prostate tissue by performing a surveillance mpMRI and MRI-TB at 12-months following FT.
2. To determine the proportion of men with CSPCa (GG ≥2) in the unablated prostate tissue by performing a surveillance mpMRI and MRI-TB at 12-months following FT.
3. To demonstrate the safety of combining ADT, and FT for the treatment of men with histopathologic diagnosis of GG 2 & 3 PCa, with PSA level < 20 ng/mL utilizing the NCI’s CTCAE v.5 classification to quantify and characterize the incidence of AEs.

Secondary endpoints

1. To define change in genitourinary and sexual function from baseline following ADT, and FT by measuring the subject’s HRQoL (I-PSS, SHIM, EPIC-26) at 6-and 12-months after FT.
2. To determine the PSA response to the combination treatment by measuring the subject’s PSA at “baseline” (PSA at time of initial diagnosis) and then at 3-months, 6-months, and 1-year from FT.
3. To determine the proportion of men converting to whole gland therapy (radical prostatectomy or radiation therapy) and/or requiring systemic therapy and/or developing metastases and/or dying of PCa during the course of study.
4. To determine the proportion of men without any PCa on any post treatment prostate biopsy.
5. To determine the proportion of men with normal baseline serum testosterone who had testosterone recovery (defined as testosterone levels >300 ng/dL) at 6-, 9- and 12-months after FT.

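### Inclusion criterion 1 admits Grade Group 2 men with PSA of 20 ng/mL, and above 20 through the positive-core branch, while both primary objectives and primary endpoint 3 confine the trial to PSA below 20

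*Protocol*

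**What the plan says.** Section 5.1 opens criterion 1 with "Subjects must have intermediate-risk PCa as defined by the below criteria", so the list beneath it is the protocol's own definition of the risk group. The list has three entries:

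- Favorable: "≤ clinical stage T2c, GG2, and PSA ≤ 10 ng/mL, and <50% positive biopsy cores with PCa".
- Unfavorable, first line: "≤ clinical stageT2c, GG2, and PSA 10-20 ng/mL, or ≥50% positive biopsy cores with PCa, or".
- Unfavorable, second line: "≤ clinical stage T2c, GG3, and PSA < 20 ng/mL".

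Primary objectives 1 and 2 (Section 3.1) both describe the population as "men with a histopathologic diagnosis of Grade Group 2 & 3, with prostate specific antigen level <20 ng/mL". Primary endpoint 3, the safety endpoint in Section 13.1, uses "histopathologic diagnosis of GG 2 & 3 PCa, with PSA level < 20 ng/mL". Primary endpoints 1 and 2 in that section give no PSA limit. The Schema reads "Histopathologic diagnosis GG 2 or, have a of GG 3 and PSA <20 ng/mL".

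Section 5.1 also requires staging imaging for unfavorable-risk men before enrollment and does not require it for favorable-risk men.

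**The concern.** The strict upper limit of 20 is attached to GG3 alone. For GG2, the eligibility text and the stated population differ in two ways: at the value 20 itself, and in the positive-core alternative, which names no PSA value at all. A site that follows criterion 1 to the letter can enroll a man whom both primary objectives place outside the trial.

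The trial has a single arm and is sized against a fixed 30% for intermediate-risk men, so there is no concurrent control group to share a shift in case mix. A man admitted this way meets the criterion as written and is not a protocol deviation on that ground. Once given ADT and focal therapy, he would stay in the ITT set and also in the per-protocol set.

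The overlap at PSA 10 is a related fault with a practical side: sites can classify the same man differently and so differ on whether he must be staged.

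**Working it through.** The protocol states no figure to reproduce on this point. The check is one of eligibility logic.

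**Grouping of the unfavorable GG2 line.** It can be read in two ways:

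- A: ≤T2c and GG2 and (PSA 10 to 20, or ≥50% cores positive).
- B: (≤T2c and GG2 and PSA 10 to 20), or ≥50% cores positive.

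Under A, the positive-core alternative has a stage and grade limit but no PSA limit. Under B, it loses the stage and grade limits too. Neither reading supplies a ceiling.

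**Cases.** Take a GG2 man at stage ≤T2c, with 40% or 60% of cores positive. For such a man A and B give the same result.

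| PSA (ng/mL) | Cores positive | Favorable | Unfavorable | PSA <20 (objectives 1 and 2, endpoint 3) | Result |
| --- | --- | --- | --- | --- | --- |
| 5 | 40% | yes | no | yes | consistent |
| 5 | 60% | no | yes | yes | consistent |
| 10 | 40% | yes | yes | yes | in both classes |
| 10 | 60% | no | yes | yes | consistent |
| 15 or 19.9 | 40% or 60% | no | yes | yes | consistent |
| 20 | 40% or 60% | no | yes | no | eligible, outside objectives |
| 20.1 or 30 | 40% | no | no | no | not eligible, consistent |
| 20.1 or 30 | 60% | no | yes | no | eligible, outside objectives |

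One common limit of <20 on every GG2 and GG3 branch removes every row marked as outside the objectives. The overlap at 10 needs its own correction.

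**Other text that might close the gap.** The lead-in to criterion 1 refers back to the same list. The exclusion criteria (Section 5.2) set no PSA ceiling. The Schema has words missing and can be read as (GG2 or GG3) with PSA <20, or as a limit on GG3 only.

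**Size.** The planned total is 51/0.90 = 56.7, rounded up to 57. One man is 1/57 = 1.75%, so one man's biopsy result can change the observed proportion by at most 1.75 percentage points. For scale only, the cryoablation series in Section 4.2 reports 5-year freedom from clinically significant cancer of 74% for intermediate-risk and 64% for high-risk men. Assume that an out-of-range man carries that 10-point difference, which the protocol does not say. Each such man would then move the expected proportion by 10/57 = 0.18 points. The hypothesized fall from 30% to 15% is 15 points.

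**Sample size.** The inputs are 0.30, 0.15, alpha 0.05, power of at least 80% and 10% attrition. None depends on the PSA range, so 51 and 57 do not change.

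**The case against.** The strongest reply is that this will hardly matter in practice. The open branch sits under an intermediate-risk heading and was probably meant for GG2 men with PSA of 10 or less and many positive cores. Registration is central: source documents are reviewed before treatment starts, and questions go to the lead investigator. Values of exactly 10 or 20 are single points, and a man at 20.0 barely differs from an undisputedly eligible man at 19.9.

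Most of this stands as an argument about size. It does not repair the text. Under Registration Procedures the lead investigator may explain a criterion but may not override it, and a man who meets the words of the criterion raises no obvious query.

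Some stronger readings are tempting, but the documents do not support them:

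- *All the primary endpoints carry the PSA limit.* Only endpoint 3 does; the two efficacy proportions do not repeat it.
- *The Schema has the same fault.* It is ambiguous, and one reading agrees with the objectives.
- *Favorable and unfavorable men face opposite imaging rules.* Imaging is not required for favorable-risk men, but it is not forbidden. Staging the man at PSA 10 satisfies both lines.
- *The 30% benchmark is breached.* Section 13.4 gives that figure for intermediate-risk men with no PSA range, so the protocol does not show that it describes a strictly below-20 population.
- *A measurable share of the trial will be out of range.* The protocol gives no basis for any count of such men.

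**Conclusion.** The contradiction is real. Criterion 1 admits GG2 men whom primary objectives 1 and 2 and primary endpoint 3 exclude: those at exactly 20 ng/mL, and those above 20 with at least 50% of cores positive. The second route is the more important because it has no upper bound, although it is probably unintended. Separately, the favorable and unfavorable classes overlap at PSA 10 when fewer than half the cores are positive, which leaves the staging requirement open for that man.

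The likely effect on the results is small. The number affected is unknown, each man is 1.8% of 57, and no bias in the primary proportion has been shown. The point rests on the wording alone and needs no assumption about recurrence. The documents do not say whether the criterion or the objectives govern, so it cannot be concluded that the criterion is the text in error. What can be concluded is that the two cannot both stand.

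**What to change.** Reconcile criterion 1 in Section 5.1, the Schema, primary objectives 1 and 2, and primary endpoint 3.

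1. State one explicit PSA ceiling and group it with every GG2 and GG3 branch, using brackets or sub-items so that the positive-core alternative cannot be read without it. The objectives as written imply <20 ng/mL. If the sponsor intends to include men at or above 20, the objectives and endpoint 3 must change instead.
2. Rewrite the Schema line as a complete sentence with the same ceiling and the same grouping.
3. Make the favorable and unfavorable PSA ranges non-overlapping at 10. The sponsor should decide which class that value belongs to, because the choice determines whether staging imaging is required.

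The cost is amendment wording and a matching change to the eligibility checklist. If the ceiling is set at <20, the trial gives up only men whom its objectives already exclude. The sample size and the analysis are unchanged.
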